**Patient information**	
Demographic information	age, sex, ethnicity (nationality/ethnic minorities), marital status, Occupation (physical and non-physical)
Medical history	the type of ACS (STEMI, NSTEMI, UA), smoking history, alcohol consumption history, history of hypertension, history of hyperlipidemia, history of chronic diseases, family history of T2DM, family history of CAD
Diagnostic testing	height, weight, body mass index (BMI), blood pressure, resting heart rate, fasting blood glucose, HbA1c, serum uric acid level, triglyceride level, total cholesterol level, low density lipoprotein level, left ventricular ejection fraction (LVEF)
PCI surgery-related information	number of diseased vessels, number of stent implantation, total length of the stent
Medication situation	statin medications (low intensity, high intensity), traditional Chinese medicine (Yes or No)

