### Statistical Analysis

Baseline demographic characteristics and study outcomes conforming to normal distribution were expressed as mean ± standard deviation. The *t*-test was used for comparison between the two groups. The measurement data not conforming to normal distribution was represented as the median (quaternary interval), and the comparison between the two groups was performed using the Mann–Whitney *U* test. Descriptive statistics will be used for the overall cohort and aggregated statistics will be calculated. Descriptive statistics are used for the entire queue and the aggregated statistics are calculated. Enumeration data were expressed as frequency or percentage, and χ*2* test was used for comparison between the two groups. Univariate analysis was conducted for all factors first, and statistical learning methods such as tree integration algorithm and Lasso regression were adopted to compare and screen related risk factors from multi-dimensional perspectives. To avoid omission of important variables, covariates with *P* < 0.01 in univariate analysis and important factors screened by statistical learning method were included in multivariate logistic regression analysis. Independent risk factors for NODAP were analyzed by progressive forward regression analysis, and the OR value of each related factor and its 95%CI were estimated. *P* < 0.05 on both sides of all tests indicated statistically significant differences.

We will evaluate the potential predictors of NODAP informed by prior literature (10, 20). The data set will be randomly divided into a training dataset and an internal validation dataset in a 5:5 ratio. We will include all a priori selected variables in the final model; the Bootstrap method was used for model internal validation in this data set. If necessary, non-normally distributed variables will be transformed using the Box-Cox transformation. The validation will be established with the same inclusion and exclusion criteria and sensitivity analyses will be performed. All analyses were performed using R3.6.1 and SPSS^®^ Statistics 21 software (IBM^®^, Armonk, NY, USA). Prism 5 (GraphPad Software Inc., San Diego, CA, USA) is used for drawing statistical graphs.

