### Sample Size

Based on prior studies and conditions of each hospital (31), the number of PCI surgical interventions is between 10,000 and 15,000 in the past 10 years and in which 6.1–11.6% patients (10, 32) may develop NODAP (at least 610 patients). For the exploratory analysis of multiple risk factors, ≥10 events per variable (EPV) are necessary to obtain sufficient degrees of freedom, with the assumption of at least 20 patients with the outcome (NODAP) per predictor variable (33). The ratio of the two groups is set to 5:5 (validation dataset: training dataset); the sample size could be calculated as 300 in both the training set and an internal validation set. The actual sample size may be larger than the calculated amount, thus it will be adjusted according to the situation.

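### With 30 candidate predictors, 300 NODAP events in the training set give 10 events per predictor, half the 20 that the sample size section assumes; the unit of the 300 is not stated

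*Protocol article*

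**What the plan says.** The Sample Size section of the protocol article starts from the expected material: "the number of PCI surgical interventions is between 10,000 and 15,000 in the past 10 years", of which "6.1–11.6% patients (10, 32) may develop NODAP (at least 610 patients" at the lower end. It then gives two thresholds in one sentence. The first is that "≥10 events per variable (EPV) are necessary to obtain sufficient degrees of freedom"; the second is introduced "with the assumption of at least 20 patients with the outcome (NODAP) per predictor variable". After setting a 5:5 split, it concludes that "the sample size could be calculated as 300 in both the training set and an internal validation set". It adds that the actual number may exceed the calculated one and will be adjusted. The unit of 300 and the number of predictors behind it are not given.

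The candidates are in Table 2, in five groups; the PCI group, for example, is "number of diseased vessels, number of stent implantation, total length of the stent". The Statistical Analysis section runs univariate analysis on all factors, adds variables found by tree methods and Lasso, and uses forward regression. It also says "We will include all a priori selected variables in the final model", again without a number.

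**The concern.** Events per predictor is the only justification offered for the study size. The section names two values for it, 10 and 20, and one result, 300. A reader cannot tell which value the result is meant to satisfy, in which data set, or for how many predictors.

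EPV describes the data in which coefficients are estimated. When variables are chosen from the data, the candidates screened count towards it, and not only those that survive. If the training half has 10 events per candidate while the text implies 20, the plan presents the model as better protected against overfitting than it is. The missing unit adds a second risk, because 300 events and 300 patients are very different studies.

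**Working it through.** **Inputs.** From the Sample Size section: 10,000 to 15,000 procedures; NODAP rate 6.1% to 11.6%; at least 610 cases; EPV of 10 (necessary) and 20 (assumed); 5:5 split; 300 per set. From Table 2: 5 demographic + 8 history + 12 diagnostic + 3 PCI + 2 medication = 30 variables.

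**Reproducing the plan's figures.** The minimum case count is 10,000 × 0.061 = 610, which matches. Three routes lead to 300 per set:

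- 610 / 2 = 305, close to 300
- 30 × 20 / 2 = 300
- 30 × 10 = 300

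All three count events. No route from the stated inputs gives 300 as a number of patients. The full requirement at 20 per predictor, 30 × 20 = 600, is not the figure given per set.

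**EPV in the training set, with 300 as events.**

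| Candidates | Count | 300 / count |
|---|---|---|
| Table 2 as listed | 30 | 10.0 |
| BMI kept, height and weight dropped | 28 | 10.7 |
| Parameters: two indicators for ACS type, systolic and diastolic pressure | 32 | 9.4 |

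Twenty per predictor appears only when the two sets are pooled: 600 / 30 = 20. Conversely, 300 events at 20 per predictor support 300 / 20 = 15 candidate parameters.

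**EPV from the projected cohort.** Events per half = procedures × rate / 2; EPV = that figure / 30.

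| Procedures | Rate | Events per half | EPV |
|---|---|---|---|
| 10,000 | 6.1% | 305 | 10.2 |
| 15,000 | 6.1% | 458 | 15.3 |
| 10,000 | 11.6% | 580 | 19.3 |
| 15,000 | 11.6% | 870 | 29.0 |

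Only the last row exceeds 20. All four rows apply the rate to every PCI procedure. Table 1 then requires ACS, no earlier diabetes, a first PCI and at least 12 months of follow-up, and lists further exclusions, so the usable numbers will be lower. The documents do not say by how much.

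**What the unit changes.** As events, 300 per set corresponds to 300 / 0.116 = 2,586 up to 300 / 0.061 = 4,918 patients per set. As patients, 300 would contain 300 × 0.061 = 18.3 to 300 × 0.116 = 34.8 events.

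**The case against.** **The stated minimum is met.** On the events reading, 300 / 30 = 10 satisfies the threshold that the section calls necessary, and the 20 can be seen as a planning margin. This stands for 30 variables, so the design does not fail its own minimum on that count. The margin of 20 is nevertheless stated as at least 20, and the training set does not have it.

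**Thirty is a count from Table 2, not a declared model size.** The table lists information to be extracted, and the final model may be smaller. With 15 or fewer predictors, 300 events would meet 20, and a condensed article may leave the number to a fuller document. This stands in part. Against it, the article says that all factors are screened, which makes 30 the fair candidate count until a shorter list is named.

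**The data set may be larger than 300 per set.** The text says so, and a records study has no reason to stop at 300. This stands. It helps only as far as the projection allows, and three of the four combinations above remain below 20 before eligibility is applied.

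**A stronger reading is tempting.** A reader might infer that 300 means patients, which would leave 18 to 35 events per set and about one event per predictor (18.3 / 30 = 0.6 to 34.8 / 30 = 1.2). The documents do not support this. The figure directly follows a case count whose half is 305 and a sentence wholly about events per variable, and the section allows for a larger sample. This reading shows why the unit must be stated; it is not evidence of how large the study will be.

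**Conclusion.** The concern holds in a limited form. At 300 training events and 30 candidates, the design delivers 10 events per predictor (9.4 to 10.7 over reasonable ways of counting), half of the 20 that the section assumes. The 20 is obtained only by counting validation events that do not enter the fit. The minimum of 10 is just met at 30 variables and narrowly missed at 32 parameters.

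This rests on three assumptions: 300 counts events, as the section's own arithmetic indicates; all Table 2 variables are candidates, as the screening step indicates; and the model is fitted in the training half, as the split indicates. The projected cohort could exceed 20 per predictor only at the top of both ranges together. The defect lies in the stated justification and the missing unit. It does not show that the available records are too few for any useful model.

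**What to change.** In the Sample Size section:

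1. State that 300 is the number of NODAP events per set, and that all eligible patients are used.
2. State that the EPV requirement applies to the data used for model fitting, and give the number of candidate parameters.
3. Use one EPV figure. Either restate it as about 10 per candidate for 30 candidates, or keep 20 and limit candidate parameters to training events / 20, which is 15 at 300 events.

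Dropping height and weight, given BMI, is an easy start. It does not reach 15 alone: 28 variables at 20 each would still need 560 training events. Further cuts should be named in advance from the prior literature that the plan already invokes.

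The cost is rewording, plus either a less favourable stated EPV or a shorter candidate list. No additional patients are needed.

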### Model Evaluation

Model evaluation will be carried out quantitatively via receiver operator characteristic (ROC) analysis (34). ROC curves will be constructed to evaluate and compare the predictive models. A ROC curve plots sensitivity and specificity at a range of threshold settings. The area under the curve provides an aggregate measure of model performance across all classification thresholds and will be used to compare predictive models.

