## Abstract

**Background:** Type 2 Diabetes mellitus (T2DM) is a major risk factor for cardiovascular diseases and increase mortality. Clinical outcomes of patients after percutaneous coronary intervention (PCI) were worse in T2DM patients than those without T2DM. New-onset diabetes after PCI (NODAP) is often observed during long-term follow-up and this further aggravates cardiovascular diseases. Several studies had focused on patients after PCI with known T2DM. Previous studies showed that impaired glucose tolerance and aging are risk factors that promote NODAP. Considering the unique characteristics of patients after PCI, we will further study relevant risk factors. We sought to investigate the potential predictors of acute coronary syndrome patients with NODAP by a multicenter retrospective cohort study.

**Methods:** This is a multicenter retrospective cohort study including patients after PCI. Clinical medical records of these patients were collected from four hospitals in different areas in China, from 2010 to 2021. Patients' demographic information, medical history, diagnostic testing, PCI-related information, medication situation will be summarized using descriptive statistics, and correlation analysis was performed on the development of new-onset diabetes. Variation will be described and evaluated using χ^2^ test or Kreskas-Wallis test. The prediction model will be verified by a validation set.

**Discussion:** A novel diabetes prediction model for patients after PCI is established, and this study can achieve advanced intervention for the occurrence of NODAP. Owing to its retrospective nature, this study has some limitations, but it will be further studied through supplement data collection or prospective study. The study has been registered for clinical trials by the Chinese Clinical Trial Registry (**ChiCTR2100047241**).

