We propose leveraging advancements in machine learning by systematically comparing different modeling approaches (21), to develop a prognostic tool for NODAP. Therefore, we put forward the following hypothesis:

Refer to common risk factors such as obesity and smoking and explore the risk factors for NODAP; probing the risk of NODAP in different types of ACS patients (STEMI, NSTEMI, and UA) is equal or not.Systematically apply several machine learning algorithms to establish a predictive model of NODAP and verify its effectiveness.In this study, we sought to investigate the potential predictors of ACS patients with NODAP and comparatively evaluate performances of these predictive models with each other, to identify which is the most accurate.

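### AUC is the sole stated criterion for ranking the models, and AUC alone cannot show which prognostic model is the most accurate

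*Protocol article*

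**What the plan says.** All places are in the protocol article.

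- **Model Evaluation** gives the method: "Model evaluation will be carried out quantitatively via receiver operator characteristic (ROC) analysis". It then gives the ranking criterion: "The area under the curve provides an aggregate measure of model performance across all classification thresholds and will be used to compare predictive models". No section mentions calibration, the Brier score or any other measure of predictive accuracy.
- **Introduction** sets the aim. The plan is to "Systematically apply several machine learning algorithms to establish a predictive model of NODAP and verify its effectiveness" and to "comparatively evaluate performances of these predictive models with each other, to identify which is the most accurate". The number of algorithms is not given.
- **Abstract** (Discussion) attaches a use to the model, saying that "this study can achieve advanced intervention for the occurrence of NODAP".
- **Statistical Analysis** defines the data: "The data set will be randomly divided into a training dataset and an internal validation dataset in a 5:5 ratio". It adds that "the Bootstrap method was used for model internal validation in this data set", without saying which data set is meant or whether the bootstrap repeats the choice of model. No third set is defined.
- **Sample Size** expects 10,000 to 15,000 PCI procedures, an outcome rate of 6.1% to 11.6%, and at least 610 patients with new-onset diabetes. It arrives at 300 for each half, without saying whether these are patients or events.

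**The concern.** A prognostic tool gives each patient a predicted risk. To call it the most accurate of several is a claim about those risks, and it has two parts: whether patients are ranked correctly (discrimination) and whether the stated risks agree with what happens (calibration). AUC sees only the first. If AUC is the whole criterion, a model with distorted risks ties with, or narrowly beats, a model whose risks are right, and nothing in the stated evaluation would show it.

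The second question is what the winner's AUC means. The highest of several noisy estimates tends to exceed its own true value. With two data sets, the validation half may serve both to choose the winner and to report its performance.

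The headline claim about the best model is at stake. The odds ratios from the risk-factor analysis are not affected.

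**Working it through.** **1. The article's own figures.** Events: 10,000 × 0.061 = 610, as stated. Half is 610 / 2 = 305, close to the stated 300, so 300 fits a count of events. It also equals 20 events × 15 predictors, or 10 × 30. If 300 means patients, the events per half are 300 × 0.061 = 18.3 to 300 × 0.116 = 34.8. Both readings are carried below. The article states no AUC or calibration figure to reproduce.

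**2. What AUC cannot see.** AUC is the probability that a random patient with the outcome has a higher predicted risk than a random patient without it. It depends on rank order alone. As an illustration, 200,000 patients were simulated with a standard normal linear predictor and an intercept set for a 6.1% event rate. The true risks were then distorted without changing their order.

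| Predicted risks | AUC | Mean predicted | Observed/expected | Brier |
|---|---|---|---|---|
| True risks | 0.754 | 6.1% | 1.00 | 0.053 |
| Logit doubled | 0.754 | 1.1% | 5.51 | 0.057 |
| Linear predictor doubled, intercept kept | 0.754 | 11.8% | 0.51 | 0.070 |
| Logit + 1.5 | 0.754 | 20.0% | 0.30 | 0.081 |
| Logit + ln(0.939/0.061) | 0.754 | 41.6% | 0.15 | 0.202 |

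Giving every patient the mean risk has a Brier score of 0.061 × 0.939 = 0.057. The last three rows are worse than that, yet an AUC ranking places all five level.

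**3. Possible optimism in the winner's AUC.** Assumptions, none from the article: K = 3 or 5 models, each with true AUC 0.75; binormal scores; correlation between model scores 0.5 to 0.9; winner chosen and reported on the same validation half with no correction. Monte Carlo mean of the highest AUC minus 0.75:

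| Validation half | Excess in winner's AUC |
|---|---|
| 300 patients, 18 events | 0.017 to 0.049 |
| 300 patients, 35 events | 0.013 to 0.036 |
| 5,000 patients, 305 events | 0.003 to 0.011 |

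The approximation excess ≈ e(K) × SE × √(1 − correlation), with e(5) = 1.16, agrees. With 18 events, 1.16 × 0.0587 × √0.5 = 0.048 (simulated 0.049). With 305 events, 1.16 × 0.0127 × √0.5 = 0.010 (simulated 0.011).

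**4. Precision of one AUC.** Hanley-McNeil with A = 0.75: Q1 = A/(2 − A) = 0.600, Q2 = 2A²/(1 + A) = 0.643, and SE² = [A(1 − A) + (n₁ − 1)(Q1 − A²) + (n₀ − 1)(Q2 − A²)]/(n₁n₀). The 95% half-widths are:

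- 305 v 4,695: 1.96 × 0.0165 = 0.032
- 35 v 265: 1.96 × 0.0494 = 0.10
- 18 v 282: 1.96 × 0.0679 = 0.13

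These are intervals for a single AUC. A paired difference between positively correlated models is estimated more tightly, which is why paired intervals are the right tool for naming a winner.

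**The case against.** **A condensed article leaves detail out.** The full protocol or analysis plan may add calibration, and silence on paired intervals or resampling is not in itself an error. That is fair for those details. It does not remove the main point, because the article names its criterion and that criterion does not match its stated aim.

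**Accurate may simply mean discriminates best.** If so, AUC answers the question, but the claim should then be worded that way. A prognostic tool offered as a basis for early intervention suggests more than ranking.

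**Gross miscalibration is unlikely here.** From the table a reader might infer that the study's models will be wrong several-fold. The documents do not support this. The planned multivariable model is a logistic regression; fitted by maximum likelihood with an intercept, it reproduces the mean risk in its training data, and validation is on a random half of the same cohort. Errors in the spread of risks are more plausible if events are few, but the article requires at least 10 events per variable and assumes 20. The table shows what AUC cannot detect, not what to expect. It is also unclear which algorithms compete as final models, since Statistical Analysis uses the tree ensemble and Lasso to screen factors for the logistic model.

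**The use is modest.** The article sets no risk threshold or decision rule, and Limitations calls the analyses exploratory. This lowers the urgency, not the validity, of the point.

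**Conclusion.** The point holds for the criterion. As written, AUC alone ranks the models and that ranking is meant to identify the most accurate one. AUC cannot carry that conclusion, whatever the sample size. This rests on a mathematical property and needs no assumption about the data.

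On optimism the conclusion is conditional. A reader might infer that the winner's AUC is certain to be inflated. The article does not say that selection and reporting share data, and it plans both a held-out half and a bootstrap, which could correct the figure if it repeats the selection. The supportable statement is that the AUC may be optimistic: by about 0.01 or less if the validation half holds about 300 events, which is the reading that fits half of 610, and by roughly 0.01 to 0.05 if it holds about 300 patients. These sizes rest on the assumed number of models, their correlation and a true AUC of 0.75.

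**What to change.** In Model Evaluation:

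1. Assess each model in the validation data on calibration (intercept, slope and smoothed curve) and Brier score as well as AUC. Base the choice of the most accurate model on these together, and state beforehand how they will be weighed. If AUC alone is kept, describe the winner as the best discriminating model.
2. Report paired bootstrap or DeLong confidence intervals for the differences in AUC.
3. In Statistical Analysis, name the data set that the bootstrap uses and repeat the model-selection step within each resample, so that the chosen model's performance is corrected for optimism.

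The cost is a few sentences and a little more analysis work. No further data are needed.

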### Data Storage and Management

Protocols regarding data security have concluded between the research group and each hospital. Data will either be stored in structured query language form and entered into the third-party electronic platform. Data transfer and entry were carried out by the professional database engineer who also responsible for regular data quality checks. For data safety and security, the electronic data will be maintained under secured password-protected conditions, and access will only be given to licensed personnel (research group). Each patient will be reset a unique identification code fit for both outpatient and inpatient records. The code-breaking information will be kept separate from the data extraction files and inaccessible to individuals outside the research team and will only be available to the research group.

All electronic documents and data will be protected by passwords on the network in the platform. The required data will be exported in Excel format and further analyzed.

## Discussion

### Strengths

The protocol for the study design and methods to evaluate a new model of patients with new-onset diabetes mellitus after PCI. This study represents the largest cohort study that addresses risk factors for NODAP and it will make available data as regards blood glucose management and T2DM risk prediction. Prior studies carried out in Taiwan (20) were based on a health insurance database and the use of statin was the only variable that was extracted; all subjects in the large academic tertiary care hospitals can be a source of bias. With increases in aging, more people will be diabetic after PCI over a long period. This proportion will continue to increase, emerging sensitive predictors (35). This is the first study that addresses the risk factors for diabetes after PCI. The related factors of PCI surgery were reviewed, and a more comprehensive evaluation of diabetes after PCI was performed.

A future direction for the study is to collect patient-reported outcomes through the questionnaires to supplement the retrospectively available data, or to conduct a prospective cohort study where data will be collected at baseline and at 12-month follow-up, pending additional institutional review board (IRB) approval. Consent forms will be distributed to participants before data collection. Consent forms will highlight the voluntary nature and anonymity of the participation. Based on the above studies, our study went further to verify the risk factors, incidence and prognosis of T2DM after PCI.

